### Implementation outcomes

A descriptive analysis will be conducted for the implementation outcomes. This study is not powered to assess group differences but rather to understand the pre-post facilitation training differences in implementation outcomes of feasibility, acceptability, and appropriateness. This evaluation will utilize a mixed methods design with a Qualitative + QUANITATIVE structure that serves the function of for complementarity [40].

The qualitative aspect of the study allows for an understanding of the processes associated with the study. The monthly phone calls will be coded using a deductive content analysis [25]. Identifying information from the interviews will be removed and the interviews will be coded based on context, facilitation and strategies, and outcomes. This will be informed by iPARIHS (context and facilitation), ERIC (strategies), and outcomes (Proctor) to develop the codes. The codes will allow for information to be indexed in these relevant areas of the study and will facilitate exploration of the relevant contextual factors, interventions, and outcomes related to the study. These interviews will be co-coded by two coders in order to increase reliability of coding. Any discrepancies in coding will be resolved through meetings and discussions. Further, any order sets developed or changed will be captured and counted through these monthly phone calls.

The generalized estimating equation (GEE) model with appropriate link function will be used to analyze the implementation outcomes, in which the correlation among the ASPs from the same cluster need to be considered. The autoregressive of first order as working correlation structure will be considered. The GEE model includes the group indicator, month, and the interaction term between group and month. The *p* values of the interaction term from type 3 analysis in the GEE model will be estimated to assess whether the outcome across all ASPs between two groups are different. Least square means for each outcome for each group will be estimated and the standard errors will be calculated within the use of GEE sandwich method when accounting for within-cluster correlation.

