### Implementation data

Process: Semi-structured interviews (see Supplemental file A for interview guide) will be conducted with a member of the ASP team at each site monthly through the duration of the trial. These interviews will be conducted virtually via zoom and will last ~30 min. We will assess the progress of the site in identifying, reviewing, and changing current surgical order sets and implementing new order sets that do not contain post-operative orders for antibiotics. Furthermore, information will be obtained regarding current barriers, and additional work being done to eliminate unnecessary post-operative antibiotics (e.g., stakeholder meetings).Outcomes:
*Acceptability, Appropriateness, Feasibility*: We will assess the acceptability, appropriateness, and feasibility of each strategy using psychometrically strong and pragmatic survey measures [39], which will be distributed once during each step. All members of the ASP team will complete these surveys regarding the intervention(s) currently being implemented by the ASP. Therefore, during control, participants will complete the surveys for acceptability, appropriateness, and feasibility in relation to changing order sets as an implementation strategy. During the intervention, participants will complete separate surveys to independently evaluate changing order sets and the use of facilitation techniques.*Penetration* will be measured as the number of order sets modified or newly created. These data will be collected monthly through the web-based semi-structured interview.*Health beliefs*: Once per step, each member of the antibiotic stewardship team will be asked three health belief questions modeled off the COM-B system [18]. These questions assess the participants’ belief in their capability, motivation, and opportunity to change post-operative order sets.

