## Statistical analysis plan

### Clinical outcomes

#### Primary hypothesis

Our primary hypothesis is that the experimental intervention of enhanced ASP facilitation will decrease the percentage of cases receiving unnecessary postoperative antibiotic prophylaxis from baseline more than the control intervention. To test this hypothesis, statistical model (1) will be used. With each cross-section consisting of *m* patients, we assume a model in which the logit of outcome for patient *i* at times *t* = 0, ⋯, *T* in hospital *k* = 1, ⋯, *K*, and cluster *l* = 1, 2, 3 is
1$$ \mathrm{logit}\left({\pi}_{itkl}\right)=\gamma +{\theta}_t+{A}_{lt}\delta +{x}_{kl}+{h}_{tkl}+{\varepsilon}_{itkl}, $$

where *π*_*itkl*_ is probability of percentage of unnecessary postoperative antibiotic prophylaxis, $$ {\varepsilon}_{itkl}\sim N\left(0,{\sigma}_{\mathrm{error}}^2\right) $$, $$ {h}_{tkl}\sim N\left(0,{\sigma}_{\mathrm{time}\mid \mathrm{clinic}}^2\right) $$, $$ {x}_{kl}\sim N\left(0,{\sigma}_{\mathrm{clinic}}^2\right) $$, with *ε*_*itkl*_, *h*_*tkl*_, and *x*_*kl*_ are all independent of one another, and
$$ {A}_{lt}=\left\{\begin{array}{c}1\ \mathrm{if}\ \mathrm{cluster}\ l\ i\mathrm{s}\ \mathrm{receiving}\ \mathrm{the}\ \mathrm{intervention}\ \mathrm{at}\ \mathrm{time}\ t\\ {}0\ \mathrm{if}\ \mathrm{cluster}\ l\ i\mathrm{s}\ \mathrm{receiving}\ \mathrm{the}\ \mathrm{control}\ \mathrm{at}\ \mathrm{time}\ t\kern2.5em \end{array}\right. $$

This hierarchical, multilevel model includes a fixed effect of time *θ*_*t*_, we set *θ*_0_ = 0. The parameter *δ* is the treatment effect; we assume that the treatment effect is maintained once the intervention has been initiated. The fixed effect *θ*_*t*_ must be estimated independently of the treatment effect so that a systematic change over time is not mistaken for an effect of treatment. The model also includes random effect, variation between clusters (*x*_*kl*_), and variation between times within a hospital (*h*_*tkl*_).

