#### Secondary hypotheses

We will also test multiple secondary hypotheses to understand the additional impact of our strategy implementation. These include the following:
The rate of surgical site infection will be no different prior to the study versus order set and/or enhanced facilitation groups.The rate of *Clostridioides difficile* infection will be improved when comparing control versus baseline, and experimental condition versus control or baseline.

A statistical model analogous to model (1) will be used for the secondary outcomes analyses, where *π*_*itkl*_ will be replaced by the rate of SSI or CDI and implementation outcomes, respectively.

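### Implementation outcomes: the group comparison rests on the group-by-month interaction, which is zero under a sustained constant gain, and a second section assigns the same outcomes to a main-effect model

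*Protocol article*

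**What the plan says.** Three parts of the Protocol article bear on this.

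- **Statistical analysis plan, Implementation outcomes.** The section opens with "A descriptive analysis will be conducted for the implementation outcomes" and gives the aim as to "understand the pre-post facilitation training differences in implementation outcomes of feasibility, acceptability, and appropriateness". It adds that the study is not powered for group differences. It then specifies: "The GEE model includes the group indicator, month, and the interaction term between group and month". Whether the two groups differ is to be judged by the type 3 p "values of the interaction term from type 3 analysis in the GEE model will be estimated to assess whether the outcome across all ASPs" differs between them. It also says "Least square means for each outcome for each group will be estimated", with sandwich standard errors, but names no contrast or test of those means.
- **Statistical analysis plan, Secondary hypotheses.** A model analogous to model (1) is to be used, in which the modelled probability "will be replaced by the rate of SSI or CDI and implementation outcomes, respectively". The treatment parameter of model (1) is a main effect, and for it the plan says "we assume that the treatment effect is maintained once the intervention has been initiated".
- **Implementation data.** The acceptability, appropriateness and feasibility surveys are measures "which will be distributed once during each step". Penetration is the number of order sets modified or created, collected monthly. The Abstract calls penetration the primary implementation outcome.

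**The concern.** The stated aim is a difference in level before and after facilitation training. The stated rule tests a difference in slope. If facilitation lifts a survey score by a fixed amount and the lift lasts, the two slopes are equal and the interaction is zero however large the lift. The p value named as the answer to whether the groups differ would then carry no information on that question.

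Two features of the design add to this. All hospitals are control in step 0 and all are facilitated from step 3, so the control slope is learned only from the early months and the facilitation slope mostly from the later ones. A secular trend that flattens can therefore look like an interaction. And since another section assigns the same outcomes to a main-effect model, two analyses with different target parameters are in force and could disagree, with no statement of which governs.

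**Working it through.** **Layout.** The plan gives no figure for this GEE to reproduce. Its one power figure serves to confirm the layout. Inputs from Study design and Power estimates: 9 hospitals in 3 clusters of 3, six-month steps over 3 years (6 periods), crossover at the start of steps 1, 2 and 3, rates 33% and 13%, ICC 0.121, cluster auto-correlation 0.328, 46 cases per step per hospital.

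- Variance: σ² = (0.33×0.67 + 0.13×0.87)/2 = 0.1671.
- Covariance of one hospital's period means: σ²·ICC·CAC in every cell, plus σ²·ICC·(1−CAC) + σ²·(1−ICC)/46 on the diagonal.
- Generalised least squares gives a standard error of 0.0713 for the treatment effect. Power = Φ(0.20/0.0713 − 1.96) ≈ 0.80, and 46 is the smallest number that reaches 80%.

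The stated figure reproduces with 6 periods, so crossovers at months 6, 12 and 18 of 36 are used below. They also match the stated 24 and 18 months of exposure for clusters 2 and 3. The 350 months printed for cluster 1 cannot be right in a 36-month trial; this layout gives 36 − 6 = 30.

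**1. Interaction under a constant gain.** Write the mean on the link scale as a + b·month + d·group. The GEE mean is β0 + β1·group + β2·month + β3·group×month. The two agree with β1 = d and β3 = 0. Fitting the layout with an assumed d = 0.5 and b = 0.01 returns group 0.5, month 0.01, interaction 0.000. Replacing month by step (6 periods, crossovers at 1, 2 and 3) also gives an interaction of 0. A monthly order-set rate that rises from 0.5 to 1.0 gives group 0.5, interaction 0.

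**2. Rejection rates.** Simulation, 500 runs per case, 9 hospitals by 36 months, linear month, AR(1) working correlation, sandwich standard errors with variance scaled by 9/8, t on 8 degrees of freedom. Assumed, since the documents give no values: Gaussian monthly outcome, hospital SD 0.3, residual SD 0.5, autocorrelation 0.4.

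| Constant gain | Interaction test | Group term, no interaction in the model |
|---|---|---|
| 0 | 7.0% | 7.0% |
| 0.3 | 5.2% | 46% |
| 0.5 | 6.0% | 90% |
| 1.0 | 4.8% | 100% |

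The right-hand column depends on the assumptions. The flat middle column follows from step 1 and does not.

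**3. Overlap and curvature.** Both conditions are present only in months 6 to 17 counting from 0, which is 12 of 36. With month as a class variable, 6 + 18 = 24 of the 72 group-by-month cells are empty. With linear month, take no facilitation effect at all and an assumed trend that rises by 1/12 = 0.083 per month for 12 months and then stays flat. The least-squares fit gives an interaction of −0.063 per month, most of the early slope, though facilitation does nothing.

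**4. Penetration as a running total.** If each hospital's cumulative count is analysed, and the assumed monthly rate rises from 0.5 to 1.0 at crossover, the interaction is 0.40 per month. Here the interaction does pick up the effect.

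**5. The two sections side by side.** Secondary hypotheses: the treatment effect is a main effect alongside fixed time effects. Implementation outcomes: it is a slope difference. In addition, the surveys come once per step, so they have no monthly series for a month term.

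**The case against.** The strongest reply has four parts.

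- **Penetration may be unaffected.** The Abstract defines it as the number of order sets changed or developed during the study, which can be read as a running total. A sustained rise in rate is then a slope difference. In a simulation of cumulative Poisson counts (rate 0.5 rising to 1.0, assumed) the interaction test rejected 44%, while a group term with categorical month rejected 9%. This stands. A reader might infer that the primary implementation outcome is necessarily judged on the wrong parameter; the documents do not settle cumulative against monthly counts, so they do not support that.
- **The constant-gain assumption belongs to model (1).** It is stated for the primary clinical outcome, and a workshop followed by monthly calls could have a growing effect, which would give a non-zero interaction. This stands in part. But a constant gain is the simplest form of the pre-post difference that the section seeks, and a test blind to it cannot carry the question of whether the groups differ.
- **The level difference would still be seen.** A reader might infer that a real improvement would have to be reported as no difference. That is too strong: least square means per group are planned, and the model (1) analogue tests a level effect. Yet no contrast of the means is named, with categorical month and empty cells the means averaged over months are not estimable, and the text does not say which model governs.
- **The analysis is descriptive and unpowered.** True, and it limits severity. It does not justify a stated p value that answers another question.

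How month is coded is a detail that a separate SAP may settle. The zero interaction under a constant gain holds for either coding.

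**Conclusion.** The point holds for acceptability, appropriateness and feasibility, and for order sets counted per month: the named test has no power beyond its null rate against a sustained constant gain. That result is algebraic and rests only on the gain being constant on the link scale. The 46% to 100% for the group term, and the −0.063 per month from a plateauing trend, illustrate assumed inputs. The point does not hold for penetration analysed as a cumulative total. The conflict between the sections on secondary hypotheses and on implementation outcomes is plain from the text and needs no assumption.

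Severity is moderate. A reader might take this as a threat to the trial's main conclusion; it is not, because the primary clinical outcome, its model and its sample size do not depend on this test.

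**What to change.** - Name one governing model for each implementation outcome, and make the sections on secondary hypotheses and on implementation outcomes agree. Do not simply strike the implementation outcomes from the former: as written it is the only text that tests a level effect.
- Enter time as a main effect: step for the once-per-step surveys, month for penetration.
- Base the comparison on the group coefficient, with a confidence interval and a small-sample correction for nine hospitals.
- Analyse penetration as order sets changed or created per month, not as the running total, so that the group coefficient is a rate difference or rate ratio.
- Keep the group-by-time interaction only as a secondary description of change over time.

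The cost is wording; no data collection or sample size changes. The downside is that an effect that grows over time is summarised as an average, which the secondary interaction can describe.

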## Discussion

The proposed research will develop and evaluate de-implementation strategies to eliminate unnecessary postoperative antibiotic use in pediatric surgical cases. Two strategies, order set review and modification, and order set review and modification plus enhanced facilitation, will be compared. These strategies have been successful in previous healthcare implementation efforts but have not been directly compared [19, 43–46]. As each hospital receives their facilitation training, we hypothesize that participants’ beliefs in this process will improve. Important clinical outcomes including antibiotic use, CDI infection, and SSI infection will be assessed. If effective, these de-implementation strategies will support the reduction of overall antibiotic overuse, decrease the incidence of CDI, and will help maintain the effectiveness of our antibiotic arsenal for the future. The insights and information learned will help in the development of future strategies to de-implement other unnecessary medical practices.

De-implementation has become a prevalent area of study in implementation science, but there remains a lot to be learned about de-implementation mechanisms and strategies, especially in healthcare settings [47, 48]. This study will contribute to the implementation science literature in several ways. First, there is a need for more implementation and de-implementation strategies that are systematically designed and informed using relevant theories and frameworks [49–51]. This study will demonstrate how a number of frameworks, namely, i-PARIHS and COM-B, can inform the development and execution of a facilitation-based implementation strategy.

Second, while there is growing evidence for strategies that can influence the de-implementation off harmful and/or low-value care, there is a need for more experimental evaluations of de-implementation strategies, particularly multisite trials that rigorously evaluate their effects [52].

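### The p value named for comparing implementation outcomes tests whether the group difference changes over months, not the before-versus-after training difference, and a second model is assigned to the same outcomes

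*Protocol article*

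**What the plan says.** All places are in the protocol article.

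- Implementation outcomes gives the mean model: "The GEE model includes the group indicator, month, and the interaction term between group and month". It then names the p value by which the two groups are to be compared: "values of the interaction term from type 3 analysis in the GEE model will be estimated to assess whether the outcome across all ASPs". This is the only p value that the section names.
- The next sentence adds level estimates: "Least square means for each outcome for each group will be estimated and the standard errors will be calculated" by the sandwich method. No test or interval for the difference between these means is stated.
- The same section calls the analysis descriptive and gives its purpose: "This study is not powered to assess group differences but rather to understand the pre-post facilitation training differences in implementation outcomes".
- Secondary hypotheses states that "A statistical model analogous to model (1) will be used for the secondary outcomes analyses", and lists the implementation outcomes among those to be put in place of the primary one. Of the treatment effect in model (1), Primary hypothesis says: "we assume that the treatment effect is maintained once the intervention has been initiated".
- Implementation data says of the acceptability, appropriateness and feasibility surveys: "which will be distributed once during each step". Health beliefs are also asked once per step. Penetration, a count of order sets, is collected monthly.

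**The concern.** A before-versus-after training difference is a difference in level. The named p value addresses another question: whether the gap between conditions widens or narrows from month to month. If training raises survey scores and the gain holds, the groups differ while the interaction is zero.

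A lasting gain is a plausible pattern here. Model (1), also assigned to these outcomes, assumes it. The Discussion writes "As each hospital receives their facilitation training, we hypothesize that" beliefs will improve, which at least describes a change at training. At stake is how acceptability, appropriateness, feasibility, health beliefs and possibly penetration (the primary implementation outcome) are read. A non-significant interaction could be taken as evidence that facilitation made no difference, while the other named model shows that it did.

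**Working it through.** **The plan's own figure.** The only sample size is 46 cases per step per hospital, for the primary outcome. Inputs: nine hospitals, three sequences, ICC 0.121, cluster auto-correlation 0.328, two-sided 0.05, and variance (0.33 × 0.67 + 0.13 × 0.87)/2 = 0.1671. With six six-month periods, the generalized least squares variance for a repeated cross-section stepped wedge gives 80.05% power, and 46 is the smallest sufficient number. The figure reproduces and this point does not touch it. No figure is given for the implementation outcomes.

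**Algebra.** Let G = 1 after training, M = calendar month and g = the link. The planned model is

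g(mean) = b0 + b1·G + b2·M + b3·G·M,

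so the difference between conditions at month M is b1 + b3·M. The named test is of b3 = 0. A constant shift D on the link scale means b1 = D and b3 = 0 for every D.

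**Noiseless check.** The layout is 36 months (numbered 0 to 35), nine hospitals, and switches at months 6, 12 and 18, from six-month steps over three years. (Study design prints 350 months of exposure for cluster 1, which cannot fit in a 36-month trial and is not used.) Fitting y = 3 + 0.02·M + D·G for D = 0.5, 1, 2, 5 and 20 returns an intercept of 3, a group term of D, a month slope of 0.02 and an interaction of 0 each time. If month is a factor, both conditions are seen in months 6 to 17. That is 12 months and 12 − 1 = 11 interaction contrasts, all zero under a constant shift.

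**Simulation with monthly data.** 2,000 trials per row; AR(1) working correlation; sandwich errors by hospital; t(8) reference. Assumed: residual SD 0.7, hospital SD 0.4, AR(1) 0.5, slope 0.02 per month.

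| True shift | Interaction (planned test) | Group term at the mean month, planned model | Group term, no interaction |
|---|---|---|---|
| 0 | 7.5% | 8.4% | 6.3% |
| 0.5 | 8.3% | 45% | 64% |
| 1 | 8.5% | 91% | 99% |
| 2 | 8.1% | 100% | 100% |
| 5 | 6.7% | 100% | 100% |

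The third column is the contrast between the group least square means if they are taken at the average month. The planned fit therefore holds the information, but the plan names no test of it. Null rates above 5% reflect the nine clusters and are a separate matter.

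**Simulation with one survey per step.** Assumed: five team members per hospital; SDs hospital 0.3, hospital-step 0.2, member 0.4, residual 0.5; exchangeable working correlation; t(7) reference. For shifts of 0, 0.3, 0.5 and 1.0 the interaction rejects in 8%, 7%, 7% and 7%. The group term with calendar step as a factor rejects in 7%, 41%, 81% and 100%. With normal critical values the figures are 14%, 12%, 13% and 13% against 12%, 53%, 89% and 100%. A re-run with the plan's AR(1) structure at a shift of 0.3, under six settings of members and variances, put the interaction at 11% to 14%.

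**Where the interaction does respond.**

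- Penetration as a running total: a lasting rise in the monthly rate is a change of slope. For rises of 0.05, 0.1 and 0.2 per month the interaction rejects in 32%, 79% and 100%. The group term without interaction rejects in only 7%, 7% and 9%.
- Log link with an additive shift on a rising trend (1 + 0.03·M): the interaction is −0.0105, −0.0131 and −0.0162 per month for shifts of 0.5, 1 and 2. It is already −0.0062 with no shift, because that trend is not linear on the log scale. A multiplicative shift gives 0.

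**The two analyses side by side.** Under a constant shift, the analogue of model (1) estimates D with period effects removed, while the GEE's named test looks at a quantity equal to zero. The first can be clearly significant and the second null in the same data.

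**The case against.** The strongest reply is that the plan does not depend on this p value alone.

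- **Another model covers the shift.** The analogue of model (1) tests a lasting shift in these outcomes. This stands, so a reader who infers that a lasting benefit of any size could not be detected goes too far. What remains is that two analyses are named, no precedence is given, and the section devoted to these outcomes names the unsuitable test.
- **Levels are reported.** Group least square means with standard errors are planned, so a large shift would be visible. This also stands. It would not necessarily be reported as no difference, but no test or interval for the difference is stated. With month linear, the average month (17.5) lies just where control data end.
- **The analysis is descriptive and not powered.** True, and it lowers the stakes. It excuses low power, but not a p value aimed at a different question.
- **Penetration may be cumulative.** The abstract counts order sets over the study, which can be read as a running total, and a slope contrast then fits. The article does not say which form is analysed, so no blanket claim about penetration is justified.
- **The expected shape is inferred.** The maintained-effect assumption is written for model (1), and the Discussion gives no shape. Monthly calls follow the workshop, so gradual growth is possible, and the interaction would pick up some of it. This stands. The point is about the mismatch with the stated aim, not a prediction of the effect's form.
- **Cluster 1 has a single control survey.** Little weight belongs here, since GEE slopes are pooled across hospitals.

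**Conclusion.** The concern holds in limited form. The interaction p value named under Implementation outcomes has no power beyond its null rejection rate against a constant shift on the link scale. This follows from the algebra and does not depend on the assumed SDs; only the rejection percentages do. The test therefore does not match the section's own aim. The article also gives two analyses for the same outcomes that can disagree.

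A reader might infer that facilitation's effect on implementation outcomes would be missed altogether, or that penetration is necessarily affected. The documents support neither: the model (1) analogue and the group means would show a shift, and a cumulative count responds to the interaction. The primary clinical analysis and its sample size are untouched. The change should be made because a stated test answers a different question, but it concerns a descriptive, unpowered part of the trial.

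**What to change.** Reconcile Secondary hypotheses and Implementation outcomes so that one analysis is named for each implementation outcome.

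1. For acceptability, appropriateness, feasibility, health beliefs and any per-period penetration count, base the comparison on the group coefficient (facilitation versus control). Use a model with group and calendar step as a factor and no interaction, and report the estimate with its 95% CI.
2. Keep any interaction as exploratory, with time since training in place of calendar month.
3. State whether penetration is analysed per period or cumulatively. If cumulatively, a slope contrast may stay for that outcome.
4. Keep the statement that these analyses are descriptive and not powered.

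The cost is a few sentences of analysis wording and no new data. The small downside is that the model assumes a constant effect after training, as model (1) already does; the exploratory interaction gives some check on that.
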